### Trial design {8}

This is a randomized, double-blind, sham-controlled, multi-center clinical trial with an adaptive design and a planned enrollment of up to 446 participants, including up to 21 participants in an initial non-randomized roll-in phase. Eligible participants are randomized in a 2:1 ratio via permuted block design to receive either VIA Disc NP or sham procedure. Randomization is stratified by site and previous intradiscal biological treatment (Y/N). All participants, clinical personnel, and outcome assessors are blinded to group assignment.

The primary efficacy analysis of this superiority trial will be conducted at 12 months, with long-term efficacy, safety, and exploratory imaging data collected through 24 months. Pre-specified interim analyses will be used to guide the adaptive design while controlling type 1 error inflation and power.

Sham participants who meet crossover criteria at 12 months (visual analog scale (VAS) ≥ 40 mm and ODI ≥ 40) are eligible to receive VIA Disc NP and initiate a secondary 12-month follow-up. All procedures are standardized across sites and performed under moderate conscious sedation using a fluoroscopy-guided technique.

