### Participant timeline {13}

Participants undergo screening and baseline assessments prior to the day 0 procedure. In-person visits are scheduled at months 1, 3, 6, 12, and 24 to collect efficacy and safety data. Phone check-ins at months 9, 15, 18, and 21 gather adverse event and medication updates. The 12-month visit includes crossover evaluation for sham participants (VAS ≥ 40 mm, ODI ≥ 40). All timepoints and procedures follow the protocol schedule of events (Table 1). The participant timeline is shown in Fig. 1.

**Table 1 Tab1:** Schedule of enrollment, interventions, and assessments

Visit/assessment	Screening	VIA Disc NP procedure/randomization	1-Month visit	3-Month visit	6-Month visit	9-Month visit (phone call)	12-Month visit (sham arm crossover)	15-Month visit (phone call)	18-Month visit (phone call)	21-Month visit (phone call)	24-Month visit	Unscheduled visit
	(0–90 days prior*)	(Day 0)	(± 7 days)	(± 14 days)	(± 28 days)	(± 14 days)	(± 45 days)	(± 14 days)	(± 14 days)	(± 14 days)	(± 60 days)	
Informed consent	X^a^											
Eligibility criteria (inclusion/exclusion)	X											
Demographics and back treatment history	X											
Vital signs^b^	X	X										X
Medical history and labs (if applicable)	X											
Urine pregnancy test (for WOCBP)	X	X					X^h^					X^e^
Physical and neurological exams	X	X	X	X	X		X				X	X
MRI and evaluation	X^c^				X							
X-ray (less than or equal to 6 months from screening, AP, lateral, flexion–extension)	X^c^											
VIA Disc NP procedure		X^d^					X^h^					
Oswestry Disability Index (ODI)	X		X	X	X		X				X	
Visual analog scale (VAS)	X		X	X	X		X				X	X
EuroQol-5 Dimension (EQ-5D-5L)	X		X	X	X		X				X	
Patient global impression of change (PGIC)			X	X	X		X				X	
Concomitant medications	X	X	X	X	X	X	X	X	X	X	X	X
Opioid use assessment via PDMP							X					
Concomitant therapies	X	X	X	X	X	X	X	X	X	X	X	X
Adverse events	X	X	X	X	X	X	X	X	X	X	X	X
Study exit							X^g^				X	

*All effort should be made to complete screening within 14 days. Up to 90 days is provided in the event of delays to obtain MRI/MRS

^a^Study procedures must not be performed until after informed consent is signed

^b^Vital signs include oral temperature, sitting blood pressure, pulse oximetry, heart rate, and respiratory rate. On day 0 (day 0 visit), vital signs will be captured both pre- and post-procedure

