^c^Participants will undergo MRI and X-rays within 6 months of screening unless site is obtaining advanced imaging, which requires new images. If greater than 6 months or not available, MRI and/or X-rays must be repeated. An MRI of the lower back per the imaging protocol must be obtained within 6 months (+ 28 days) of VIA Disc NP procedure

^d^Participants should be observed for adverse reactions for 30 min post-procedure prior to discharge

^e^Urine pregnancy test should be performed if the participant is a woman of childbearing potential and suspects pregnancy

^g^Participants who do not cross over at 12 months will exit the study

^h^Sham participants with VAS ≥ 40 mm and ODI ≥ 40 may cross over and receive the VIA Disc NP treatment at the 12-month visit

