### Procedure for unblinding if needed {17b}

When it is necessary to break the blind prematurely, the researcher will be required to notify the IRB. The sponsor will be notified as soon as possible, preferably by email or telephone and then in writing, regarding the necessity of code breaking.

Blinded site personnel (e.g., clinical study coordinator, sub-investigators) will record the participant’s PROM scores at the 12-month visit. All participants will then be unblinded to original treatment assignment. Unblinding for purposes of crossover will occur as follows:Participants randomized to the sham control group with VAS ≥ 40 mm and ODI ≥ 40 at 12 months will be approved for crossover to VIA Disc NP treatment and followed for an additional 12 months.Participants in the sham control group with VAS < 40 mm or ODI < 40 at 12 months will be informed that they do not meet the criteria for crossover and will exit the trial.

All participants will proceed unblinded after the 12-month visit to study completion at 24 months.

Emergency unblinding may be necessary if a participant experiences a serious adverse event (SAE) that requires knowledge of the treatment assignment for appropriate medical management. The investigator will contact the designated unblinding contact (e.g., study monitor or medical monitor) to request unblinding. The request for unblinding will be documented, including the reason for unblinding and the date and time of the request. The unblinding contact will access the randomization list and provide the treatment assignment to the investigator. The unblinded information must be treated confidentially and shared only with those necessary for the participant’s safety.

If any blinded party becomes unblinded to treatment allocation for a particular participant, this should be recorded using the unblinding CRF. If a participant is unblinded, they will stay in the trial and be followed up as usual.

Planned unblinding will occur after all primary endpoint data have been collected at the 12-month visit. The process for planned unblinding will be documented in the statistical analysis plan (SAP). The unblinding process will be overseen by the study statistician and data management team. Once unblinding occurs, the treatment assignments will be revealed to the investigators, study team, and participants, as appropriate.

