This posterior probability is calculated using beta non-informative Jeffreys priors for both groups. Participants who receive alternative treatments during the study, e.g., epidurals or increased narcotics, will be handled analytically in the primary endpoint calculation. In the same fashion, participants who do not complete the study will be categorized by the reason for missingness and handled according to this designation. These events (additional treatments or exiting the study for specific reasons) are called intercurrent events. At a high level, participants with temporally proximate, clinically meaningful alternative treatments will have their month 12 endpoint data imputed from participants without additional treatment. This is consistent with ICH E9R1 discussion and the methodology of defining estimates of interest and intercurrent events.

For the VAS, ODI, EuroQol (EQ-5D), and patient global impression of change (PGIC) endpoints, mean change in scores at each follow-up time-analysis will be performed with the hypothesis:

H0: dt − dc ≤ 0.

Ha: dt − dc > 0.

where “dpt” is the mean change in VAS and ODI scores among the treatment (dt) and control (dc) arms, respectively. Endpoints defined as proportions will be tested by comparing differences in proportions. The tests will be conducted with the hypotheses at each follow-up interval:

H0: pt − pc ≤ 0.

Ha: pt − pc > 0.

where “pt” and “pc” are the percentage of responders in the treatment (pt) and control arms (pc), respectively, at 12 months. These analyses will be conducted for all differences in proportion endpoints including:Proportion of participants who achieve at least a 50%-reduction in VAS score for back-pain severity SCB assessed at each follow-up intervalProportion of participants who achieve a PASS, defined as a VAS score for pain severity of 30 mm or less, assessed at each follow-up intervalProportion of participants who achieve a MCID, defined as a 30% or greater improvement in ODI score assessed at each follow-up intervalProportion of participants who achieve SCB, defined as a 50% or greater improvement in ODI score assessed at each follow-up intervalProportion of participants who achieve a PASS, defined as a ODI score for back function of 20 or less at all follow-up intervalsProportion of participants in each ODI functional impairment category assessed at each follow-up interval

Secondary endpoints will be tested using both Bayesian and frequentist statistics.

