## Trial status

Enrollment commenced in July 2025 and will continue until the required number of eligible participants is enrolled in the trial which is expected to take 10 months. The participants will be followed for 24 months and an estimated timeline for the trial including subject recruitment, follow-up, and data analysis will be approximately 30 months with expected completion of the trial by December 2027.

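### Secondary treatment-versus-sham tests run to month 24, when no untreated sham participant is left; the exit wording and the completion date also need reconciling

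*Protocol article*

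**What the plan says.** **Month 12.** Procedure for unblinding if needed {17b} divides the sham arm in two. Those with VAS of at least 40 mm and ODI of at least 40 "will be approved for crossover to VIA Disc NP treatment and followed for an additional 12 months". The remaining sham participants "will be informed that they do not meet the criteria for crossover and will exit the trial". Footnote g to Table 1 (Participant timeline {13}) reads "Participants who do not cross over at 12 months will exit the study" and names no arm. Further down, {17b} states "All participants will proceed unblinded after the 12-month visit to study completion at 24 months".

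**Month 24.** Trial design {8} places the primary analysis at month 12, "with long-term efficacy, safety, and exploratory imaging data collected through 24 months". Participant timeline {13} says "In-person visits are scheduled at months 1, 3, 6, 12, and 24 to collect efficacy and safety data", and Table 1 marks VAS, ODI, EQ-5D-5L and PGIC at month 24.

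**Tests.** Outcomes {12} lists the secondary efficacy endpoints for each follow-up interval. Statistical methods {20a} sets one-sided treatment-minus-control hypotheses for the mean changes at each follow-up time. For the responder endpoints it says "The tests will be conducted with the hypotheses at each follow-up interval", and then defines the two responder percentages as those at 12 months.

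**Timeline.** Trial status gives enrolment from July 2025 lasting 10 months, 24 months of follow-up, a total of about 30 months including data analysis, and "expected completion of the trial by December 2027".

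**The concern.** A treatment-versus-sham test needs a sham group that has not had the treatment. The month-12 rules remove that group, but the test plan makes no exception for month 24. If the plan is followed literally, the month-24 test either has no sham data or uses sham-randomised people who have since received VIA Disc NP. A p-value or posterior probability from the second option would look like a randomised 24-month comparison and would not be one.

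The statements on who stays after month 12 also disagree, so a reader cannot tell from the text which month-24 data set is intended. The stated duration is shorter than the sum of its parts.

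**Working it through.** **1. Who is in the sham arm at month 24?** With 2:1 allocation, the sham arm is N/3. Sample size {14} gives N from 248 to 446.

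- 248/3 = 82.7, about 83.
- 446/3 = 148.7, about 149. If the maximum includes the 21 roll-in participants, as {8} says, then (446 − 21)/3 = 141.7, about 142.

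Each sham participant falls into one of three groups at month 12:

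| Sham participant at month 12 | Rule | Untreated at month 24? |
|---|---|---|
| Meets criteria, crosses over | {17b} | No, received VIA Disc NP |
| Meets criteria, declines | footnote g | Not followed |
| Does not meet criteria | {17b} | Not followed |

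The untreated sham count at month 24 is therefore 0 of about 83 to 149.

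**2. What would the month-24 test compare?** The only sham-randomised people with month-24 data are those who crossed over. The contrast is VIA Disc NP at 24 months against VIA Disc NP about 12 months after crossover. The second group is selected on month-12 scores at or above 40 on both scales, which are also the lower entry limits. They have persistent symptoms but are not exactly the non-responders: someone who entered at VAS 90 and is at 40 has improved by (90 − 40)/90 = 56% and still meets the VAS part. By {17b}, everyone is unblinded by then, and all four outcomes are patient-reported.

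**3. Does the sentence keeping all participants to month 24 rescue the test?** If it overrode the sham exit rule, the untreated sham participants at month 24 would be those below 40 on at least one scale at month 12, plus any who declined crossover. That is a group selected mainly for doing well, so the contrast would still not be the randomised one.

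**4. Which visits are affected?** Efficacy visits are months 1, 3, 6, 12 and 24; the calls at months 9, 15, 18 and 21 collect adverse events and medication updates. Month 24 is the only efficacy visit affected.

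**5. Duration.** The stated figures agree with each other: July 2025 plus 30 months is January 2028, in line with December 2027. They do not agree with their components:

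- Accrual + follow-up = 10 + 24 = 34 months, before any analysis time.
- Enrolment start 1 July 2025: accrual ends 1 May 2026, last nominal month-24 visit 1 May 2028.
- Enrolment start 31 July 2025: accrual ends 31 May 2026, last nominal visit 31 May 2028.
- With the 60-day window: 2 March to 1 April 2028 at the earliest, 30 June to 30 July 2028 at the latest.

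Under uniform accrual over 304 days (an assumption), a nominal month-24 date after 31 December 2027 means enrolment after 31 December 2025:

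- Start 1 July: 121/304 = 39.8% (99 of 248; 178 of 446).
- Start 31 July: 151/304 = 49.7% (123 of 248; 222 of 446).
- With every visit 60 days early: 61/304 = 20.1% to 91/304 = 29.9%.

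These are shares of all enrolled participants, before anyone leaves at month 12.

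**The case against.** The strongest reply is that the controlled claims all sit at month 12: primary efficacy, primary safety, the superiority rule and the cumulative responder analysis. {8} says only that longer-term data are collected, and the Objectives speak of tracking adverse events over 24 months. A reader might infer that the protocol promises a controlled 24-month durability claim; no sentence says so. This stands, and it limits the point to secondary tests.

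{20a} also defines the responder percentages at 12 months. That could be read as confining those tests to month 12, but it follows directly on a statement that they are run at each interval, and the endpoint list after it repeats the interval wording. The mean-change tests carry no such qualifier. The phrase adds an inconsistency and does not clearly exempt month 24. Handling of post-crossover data may well be left to an analysis plan that is not shown, and the Discussion concedes analytical complexity from the crossover. Neither removes the instruction that is printed.

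Three stronger readings are tempting and are not supported:

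- *Footnote g removes the VIA arm at month 12.* It names no arm, so taken literally it does. But its column is headed as the sham crossover visit, neighbouring footnote h concerns sham participants only, {17b} gives the exit rule to the sham group, and Table 1 schedules visits and a second study exit to month 24. It is a wording slip. In the same way, the sentence keeping all participants to month 24 may mean those remaining.
- *Month-24 values will be imputed for people who left.* The imputation in {20c} is stated for missing month-12 data.
- *Follow-up will be cut off in December 2027.* The date is an expectation, and the same section commits to 24 months of follow-up.

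**Conclusion.** The point holds for the secondary between-arm tests at month 24. On the sham exit and crossover rules, 0 of about 83 to 149 sham participants supply an untreated month-24 outcome, so the randomised contrast cannot be estimated there. This rests on {17b} together with footnote g and needs no distributional assumption. Months 1, 3, 6 and 12, the primary efficacy and safety endpoints and the sample size are unaffected.

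The exit statements conflict in wording and must be reconciled; they do not show that the VIA arm is lost. The timeline is wrong on its own figures: at least 34 months against about 30, with last nominal month-24 visits around the end of April to May 2028. That about 40% to 50% of participants reach nominal month 24 after December 2027 depends on uniform accrual and on the start day within July 2025.

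**What to change.** - In {12} and {20a}, limit treatment-versus-sham tests to months 1, 3, 6 and 12, and make the responder definitions match those visits.
- Report month 24 descriptively within the VIA arm, as change from baseline.
- Report crossover participants as a separate cohort with month 12 as their baseline.
- End sham safety comparisons at crossover. The additional safety measures in {12} state no time point and need one.
- Reconcile footnote g and the sentence keeping all participants to month 24 with the sham exit rule in {17b}, naming the arm each applies to. If any untreated sham participants are kept to month 24, report them separately as a selected group.
- Reconcile the accrual period, follow-up, total duration and completion date in Trial status. On the present accrual and follow-up figures, month-24 visits run to about May 2028, up to 60 days later with the window, with analysis time to add.

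The cost is wording in the protocol and analysis plan, best settled before month-24 data exist. No visit, procedure or participant is added. What is given up is a set of month-24 secondary tests that this design cannot support.

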**Fig. 1 Fig1:**
[figure not shown]
Participant timeline

### Sample size {14}

The sample size for this study is based on a sham success rate assumption of 40% and varying superiority assumptions (delta) from 12.5 to 30 percentage points [17]. For initial study planning purposes, a frequentist *Z*-test for two proportions framework with pooled variance was used to calculate the required sample size to achieve 85% power using a one-sided alpha = 0.025 and 2:1 randomization.

Table 2 shows that when VIA Disc NP performance is 20 percentage points better than sham, *N* = 248 subjects are needed before loss to follow-up (LTFU). When VIA Disc NP performance is 15 percentage points better than sham, *N* = 446 subjects are needed (before LTFU). These sample sizes (*N* = 248 and *N* = 446) are the minimum and maximum number of subjects that will be enrolled (before LTFU).

**Table 2 Tab2:** Range of sample size estimates based on MCID responder rate differences

Sham	Treatment	Delta	*N* (no LTFU)	*N* w/LTFU
40.0%	70.0%	+ 30.0%	107	119
40.0%	60.0%	+ 20.0%	248	276
40.0%	57.5%	+ 17.5%	326	362
40.0%	55.0%	+ 15.0%	446	496
40.0%	52.5%	+ 12.5%	641	712

### Recruitment {15}

The study will include adult participants, 22–85 years of age, with symptomatic moderate to severe DDD that is not adequately resolved by non-surgical standard care. Participants will be recruited through the clinical practices of participating investigators, IRB-approved local advertising, and referrals. Enrollment will commence in July 2025 and will continue until the required number of eligible participants is enrolled in the trial. Recruitment will take place at the aforementioned 20 institutions, where eligible participants will be identified and approached by trained research staff. Inclusion and exclusion criteria will be strictly followed. The recruitment period is expected to last 10 months.

## Assignment of interventions: allocation

### Sequence generation {16a}

Participants in the randomization stage will be randomized to the VIA Disc NP group or the sham control group in a 2:1 ratio via permuted block randomization with randomization stratified by clinical site and previous intradiscal biological treatment (Y/N). The randomization allocation schedule will be prepared in advance by an independent statistician not involved in the conduct of the trial. The randomization schedule will be generated using a validated randomization software (e.g., SAS, R, or another secure randomization tool).

Randomization will occur at the time of the day 0 visit after all eligibility criteria have been evaluated and the ICF is signed. Randomization may be performed using the appropriate module in the electronic data capture (EDC) system.

### Concealment mechanism {16b}

Each participant will be assigned a unique identification number upon enrollment. The randomization list will be securely stored and accessed only by authorized personnel responsible for assigning treatment codes. Treatment assignments (e.g., VIA Disc NP, sham injection) will be coded to ensure blinding and will be provided via a secure, web-based randomization system.

To protect against selection bias, the randomized treatment allocation is blinded. Thus, treatment assignment is concealed until the day of the procedure. This serves to eliminate the risk of pre-selecting certain patients for one group or the other by knowledge of upcoming treatment assignments.

### Implementation {16c}

The EDC system will only allow unblinded site personnel to complete the randomization form. They will be able to see the randomization treatment but blinded staff will only see the randomization number (no treatment assignment). Treatment allocation is provided on the day of the procedure by unblinded personnel to the unblinded physician performing the procedure.

## Assignment of interventions: blinding

### Who will be blinded {17a}

The following individuals will be blinded:Participants: when randomized into the trial, the patient will consent to be blinded to the type of treatment they will receive until the 12-month visitOutcome assessorsClinicians (sub-investigators) completing the physical or neurological examinationStudy coordinators administering PROMs and collecting other participant data

The treating investigator will be unblinded because they are performing the procedure; therefore, a different blinded sub-investigator will complete the follow-up assessments (physical exam, neurological exam) prior to unblinding at the 12-month visit. A blinded study coordinator may administer the questionnaires. The procedure case report forms (CRFs) for both treatment groups will be identical in the EDC system. IP accountability will be maintained separately. To assess the fidelity of the blinding, all participants will be queried immediately post-procedure and at the 12-month follow-up visit as to whether they believed they received the IP or sham.

### Procedure for unblinding if needed {17b}

When it is necessary to break the blind prematurely, the researcher will be required to notify the IRB. The sponsor will be notified as soon as possible, preferably by email or telephone and then in writing, regarding the necessity of code breaking.

Blinded site personnel (e.g., clinical study coordinator, sub-investigators) will record the participant’s PROM scores at the 12-month visit. All participants will then be unblinded to original treatment assignment. Unblinding for purposes of crossover will occur as follows:Participants randomized to the sham control group with VAS ≥ 40 mm and ODI ≥ 40 at 12 months will be approved for crossover to VIA Disc NP treatment and followed for an additional 12 months.Participants in the sham control group with VAS < 40 mm or ODI < 40 at 12 months will be informed that they do not meet the criteria for crossover and will exit the trial.

All participants will proceed unblinded after the 12-month visit to study completion at 24 months.

Emergency unblinding may be necessary if a participant experiences a serious adverse event (SAE) that requires knowledge of the treatment assignment for appropriate medical management. The investigator will contact the designated unblinding contact (e.g., study monitor or medical monitor) to request unblinding. The request for unblinding will be documented, including the reason for unblinding and the date and time of the request. The unblinding contact will access the randomization list and provide the treatment assignment to the investigator. The unblinded information must be treated confidentially and shared only with those necessary for the participant’s safety.

If any blinded party becomes unblinded to treatment allocation for a particular participant, this should be recorded using the unblinding CRF. If a participant is unblinded, they will stay in the trial and be followed up as usual.

Planned unblinding will occur after all primary endpoint data have been collected at the 12-month visit. The process for planned unblinding will be documented in the statistical analysis plan (SAP). The unblinding process will be overseen by the study statistician and data management team. Once unblinding occurs, the treatment assignments will be revealed to the investigators, study team, and participants, as appropriate.

